## **7.5. Withdrawal and termination of the study**

### ***Reasons for Withdrawal***

All participants will be encouraged to continue in the study. A participant may voluntarily discontinue from the study at any point.

Participants may be withdrawn from the study if:

1. the participant or legal representative withdraws the consent;
2. the investigator considers that further participation would have negative effects on the woman's health;
3. the participant became pregnant.

Participants who are discontinued from the study will not be re-screened.

### ***Handling of Withdrawals***

Reasons for discontinuation from the study, date and time will be documented in the patient file and recorded on the study Case Report Form (CRF). When early discontinuation from the study due to safety reasons occurs, every reasonable effort will be made to conduct all procedures or at a minimum, participants will be seen for a final evaluation and will be followed up for safety reasons. When a participant becomes pregnant during the study, the participant will be followed up until the conclusion of the pregnancy and the outcome of the pregnancy will be documented in the patient file and reported on a study specific form.

When a participant or legal representative withdraws the consent, no additional procedures will take place.

In this study, a participant will be considered lost to follow-up at study closure if she discontinued study visits without informing the study staff and cannot be traced. Participants who miss visits but do return to the study clinic prior to study closure will not be considered lost to follow-up but as having discontinued CVR use. Participants who inform the study staff that they are terminating their participation in the study will be considered early withdrawals. Contact attempt and procedures will be conducted according to the study specific RU SOP for Study Participant Retention.

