| Social Science Component | To assess the level of acceptability and reported adherence to intermittent and continuous CVR use in women in Rwanda.              | Lost to follow up rate; rate of discontinuation (base on clinical trial data).
Level of adherence based on self-reported adherence scale and diary cards.
Qualitative description of user experiences, relationship attributes, and sexual encounter attributes.
Reported vaginal practices and beliefs regarding menstruation and impact on ring adherence.
Reported reproductive health symptoms and impact on adherence.
Number of women envisaging future use of contraceptive ring. |
| Study Method             | Secondary objectives                                                                                                                | Secondary endpoints                                                                                                                                                                                                                                                                                                                                                                                                                                                                                     |
| Clinical Trial           | To assess the general safety of the CVR.                                                                                            | Incidence of self-reported vaginal symptoms and clinician-observed signs
Incidence of BV.
The numbers of women prematurely withdrawing from the study or discontinuing ring use.
Incidence of adverse and serious adverse experiences .
The numbers of incident STIs and candidiasis.
Nugent scores and Ison & Hay grading of the vaginal flora.                                                                                                                                         |

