#### **8.1.2. Enrolment visit (at the start of week 1)**

Women will be invited for the enrolment visit which will take place on the first day of their menstrual cycle. (ie. the first day of menstrual bleeding). A visit window of + 1 day will be allowed when the menstrual cycle starts on a Sunday or bank holiday. The visit can be rescheduled maximum once if the participant is not on her first day of menstrual bleeding (+ 1 day).

All test results from the baseline visit will be reviewed, and eligibility will be confirmed. Eligible women will be randomized either to an intermittent regimen (group A) or an extended (continuous) regimen (group B) of ring use.

There will be no re-screenings.

The following procedures will also be carried out:

- The general physical examination will be performed as at baseline.
- All women will be offered risk reduction counselling and condoms free of charge.
- A urine sample will be obtained for pregnancy testing.
- Study staff will teach women how to use the ring and study participants will be asked to insert the ring while still at the study clinic.

- A questionnaire on acceptability of the ring after the ring has been inserted.
- Participants will receive a diary card and will be explained how to complete a diary card regarding ring use and sexual behaviour as well as how to complete a self-rating adherence scale.
- Provide a follow-up visit date: 3 weeks after the enrolment date.

### 8.1.3. Follow up visits: Visits 2 to Visits 6

The follow up visits are planned to coincide with times of removal and insertion of the ring. Women in group A will visit the clinic at days of removal and insertion. These visits will coincide in group B as the old ring will be replaced by a new one at the same visit.

Participants in group B will be allowed to complete each follow-up visit up to three days prior/after their scheduled visit. The visit window for participants in group A (intermittent use) will depend of the kind of visit. Ring removal visits can be delayed for a maximum of 2 days, ring insertion visits can be performed a maximum of 2 days in advance. Every effort should be made to ensure participants adhere to this visit schedule.

The following procedures are performed at each ring removal visit (both study arms):

- Information on adverse events, social harms and concomitant medication will be collected.

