#### **8.1.6. Missed Visits**

Clinic staff will obtain contact information for each participant. In the event that a participant missed a scheduled appointment, study staff will immediately try to establish communication with the participant in accordance with the RU retention SOP. Mediums for contacting a participant should include only those approved by the participant beforehand, and should be implemented in such a way as to protect her confidentiality and privacy. All attempts to contact participants will be documented on the participant's contact form which is kept in the Outreach Manager's office until study completion. The need to complete all scheduled follow-up visits will be emphasized to all study participants at every visit. If the participant misses a scheduled visit but comes back outside the visit window for an unscheduled visit, she will receive additional counselling, will be asked to use dual protection and will receive a new appointment schedule.

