#### **11.1.1. Study Objectives and Variables of Interest**

The primary and secondary objectives of this clinical trial are to assess the impact on the vaginal microbiome of the use of a vaginal ring intermittently (3 weeks followed by 1 week off) or continuously (primary objective), to assess the general safety of the CVR (secondary objective 1), to assess vaginal biofilm formation and, to detect the presence or absence of a biofilm on the CVRs after intermittent or continuous use (secondary objective 2), and to determine the impact of intermittent or continuous use of the CVR on markers of inflammation and immune activation in the vagina (secondary objective 3).

The objectives will be reached by describing and comparing the variables of interest in women randomized to either intermittent vaginal ring use (group A) over a 12 week study period or continuous ring use (group B) over a 13 week study period.

The variables of interest are:

*Primary:* Changes from baseline (pre-ring use) in vaginal bacterial counts and in the absence/presence of BV-related bacteria as measured with quantitative real time PCR. Specifically, the flora species under study will include (but may not be limited to) the following species

- a. Total *Lactobacillus* count
- b. *Lactobacillus crispatus*
- c. *L. iners*
- d. *L. jensenii*
- e. *L. gasseri*
- f. *L. vaginalis*
- g. *Atopobium vaginae*
- h. *Gardnerella vaginalis*

*Secondary:*

1. Incidence of self-reported vaginal symptoms and clinician-observed signs  
Specifically:
  - a. Incidence of self-reported urogenital symptoms: any ring-use emergent cases of irritation, burning, itching, discharge, bleeding, pain
  - b. Incidence of genital signs on examination: any ring-use emergent cases of vaginal discharge, erythema, edema, ulcer, condyloma, petechia, ecchymosis, peeling
2. Incidence of BV as defined as a Nugent score >6
3. The numbers of women prematurely withdrawing from the study or discontinuing ring use
4. Incidence of adverse experiences during ring use and serious adverse experiences during or within 7 days after ring use
5. The numbers of incident STIs (HIV, HSV-2, Syphilis, Trichomoniasis, Chlamydia, Gonorrhea) and candidiasis
6. Nugent scores and Ison & Hay grading of the vaginal flora
7. Changes in phenotype of BV-related bacteria: specifically
  - i. Presence of dispersed forms of bacteria
  - ii. Presence of adhesive forms of bacteria on epithelial cells

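### Section 7.5 counts women who miss visits and return as having discontinued the ring, while section 8.1.6 reschedules them, so the discontinuation endpoint can include continuing users

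*Protocol*

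**What the plan says.** Section 7.5, under Handling of Withdrawals, sets out three outcomes for women who stop attending. A woman who cannot be traced is lost to follow-up. A woman who tells staff that she is leaving is an early withdrawal. Between these stands the rule at issue: a woman who misses visits but comes back before the study closes "will not be considered lost to follow-up but as having discontinued CVR use". The sentence sets no minimum number of missed visits, no length of gap and no condition on ring use.

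Section 8.1.6 covers this situation: "If the participant misses a scheduled visit but comes back outside the visit window for an unscheduled visit". She receives extra counselling, "will be asked to use dual protection and will receive a new appointment schedule".

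The classification feeds two endpoints. Secondary endpoint 3 in section 11.1.1 is "The numbers of women prematurely withdrawing from the study or discontinuing ring use", and section 11.1.2.4 compares study and ring-use withdrawals between the randomized groups by Fisher's exact test over the full study period. In section 6 the primary endpoints of the social science component begin with "Lost to follow up rate; rate of discontinuation", to be taken from the clinical trial data.

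Visits and windows differ by group (sections 8.1.3 and 8.1.8). Group A has five ring visits after enrolment (V2 to V6). For this group, "Ring removal visits can be delayed for a maximum of 2 days", and insertion visits may be up to 2 days early. Group B has four ring visits (V2 to V5), each with three days' leeway either side.

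**The concern.** Section 7.5 uses attendance as a stand-in for product use. A woman who comes late for one appointment, with the ring still in place or re-inserted on her return, is a discontinuer under section 7.5 and a rescheduled participant under section 8.1.6. One event has two statuses, and site staff have no rule for choosing between them. The trial is open label, so they would choose knowing the group.

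At stake is the meaning of the discontinuation figure. It is offered both as a safety measure and as a leading measure of acceptability in a setting where, according to section 4.1, acceptability of such rings has not been studied. A count that mixes late attenders with women who gave up the ring answers neither question. The same label could also enter the tabulation of discontinued women by reason and visit in section 11.1.2.2.

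**Working it through.** The plan states no figure for this point, so there is nothing to reproduce. The check has two parts.

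**1. The two rules side by side**

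| | Section 7.5 | Section 8.1.6 |
|---|---|---|
| Trigger | misses visits, returns before study closure | misses a scheduled visit, returns outside the window |
| Condition on ring use | none | none |
| Consequence | counted as having discontinued the ring | counselling, dual protection, new appointments |

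Every woman who meets the second trigger before closure can also meet the first. Section 8.1.6 does not say outright that ring use goes on, but a new schedule and advice to use a second method make little sense for a woman who has stopped.

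**2. How large the false count could be**

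Inputs from the protocol: 60 women per group; 5 ring visits in A and 4 in B. Assumptions, because the protocol gives no figure: a risk m of 2% or 5% of missing each visit, equal in both groups, independent between visits, and no true discontinuation.

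Share labelled as discontinued = 1 − (1 − m)^k, where k is the number of visits.

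| m | A (k = 5) | B (k = 4) |
|---|---|---|
| 2% | 1 − 0.98^5 = 9.6% (5.8 of 60) | 1 − 0.98^4 = 7.8% (4.7 of 60) |
| 5% | 1 − 0.95^5 = 22.6% (13.6 of 60) | 1 − 0.95^4 = 18.5% (11.1 of 60) |

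The range is about 8% to 23%. Over both groups it is roughly 10 women of 120 at 2% and 25 of 120 at 5%, with nobody having stopped.

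**Sensitivity to which visits count.** V3 and V5 in group A are insertion visits after the ring-free week. A woman who misses one has no ring in place. If only visits reached with a ring in place are counted, k is 3 in A and 4 in B. At m = 5% this gives 1 − 0.95^3 = 14.3% in A against 18.5% in B, and the order of the groups reverses.

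**The case against.** The best defence is context. The sentence stands under Handling of Withdrawals, between the definitions of loss to follow-up and early withdrawal, and speaks of visits in the plural. It may have been meant only for women who stopped attending and reappeared late, whereas section 8.1.6 speaks of one missed visit. On that reading the two rules concern different women. The reading is possible, but the text does not contain the limit that it needs.

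It is also fair to say that the primary microbiome endpoint does not use this classification, that section 11.1.2.1 keeps every woman who inserted a ring in her randomized group, that adherence is measured separately by scale and diary card, and that the quantitative social science analysis is largely descriptive (section 11.2). All of this limits the consequence. It does not remove the contradiction, which is a stated rule and not a detail left for the statistical analysis plan.

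A reader might go further and infer that the rule inflates discontinuation more in group A, with more visits and narrower windows, and so makes continuous use look better accepted. The documents do not support that. Two of A's five visits are reached with no ring in place, and leaving them out reverses the gap at equal risk. A's narrower windows push the other way by an unknown amount. At equal risk with five and four visits, Fisher's test would be significant in only 2.7% (m = 2%) to 5.3% (m = 5%) of trials with no true difference. A large imbalance needs a much higher miss risk per visit in A, for which the protocol gives no figure.

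**Conclusion.** The point holds as a contradiction between sections 7.5 and 8.1.6 that reaches two named endpoints. Applied as written, section 7.5 counts women who still use the ring as discontinuers and so overstates discontinuation. The 8% to 23% is an illustration that rests on the assumed 2% to 5% risk per visit, independence between visits and no true discontinuation; the true size depends on attendance. The misclassification may differ between groups because visit numbers and windows differ, but no claim about which group is affected more, or which regimen is favoured, can be made from the protocol. A woman in group A who misses an insertion visit does have a real interruption; that is still not a discontinuation if she resumes. The change should be made, but the primary analysis does not depend on it.

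**What to change.** - In section 7.5, keep the statement that returning women are not lost to follow-up, and replace the rest of the sentence with a statement that they are classified by documented ring use. Simply deleting the clause would leave them with no stated disposition. Add a cross-reference so that sections 7.5 and 8.1.6 agree.
- In section 11.1.1, define ring discontinuation for secondary endpoint 3 as: ring use stopped and no ring inserted again before the planned end of ring use for that regimen. Base it on diary cards, visit records and returned rings. Do not require re-insertion on schedule, because a late re-insertion would then be counted as a discontinuation again.
- Use the same definition for the rate of discontinuation in section 6.
- Report missed visits, out-of-window visits and temporary interruptions separately, by group, as adherence measures.

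The cost is a few sentences of protocol text. The diary cards, visit records and returned rings are already collected, so no new data are needed.

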### ***Termination of Study***

If the study is prematurely terminated or suspended, the Sponsor will promptly inform the investigators/institutions involved in the study, the ethics committees, and the Rwanda Ministry of Health of the termination or suspension and the reason(s) for the termination or suspension. The Rwanda-based PI is responsible for informing active study participants of study termination or suspension.

## **8. STUDY PROCEDURES**

### **8.1. Study/visit schedule**

Also refer to schedule of assessments 8.1.8.

#### **8.1.1. Screening**

The screening process is in two parts and can take up to six weeks.

##### 8.1.1.1. Pre-screening visit

RU will contact participants from previous studies who were willing and interested to participate in other studies. These women have previously consented to being contacted by RU staff, have indicated their preferred method of contact (in person at home or at work, by phone, etc.), and have provided their contact information. Standard RU procedures will be used to ensure that confidentiality is not breached. For example, the project vehicles do not carry a logo, outreach staff do not wear uniforms, and no information about the study is given to anyone other than the potential participant herself. If the target number is not reached by using this pool of potential participants, women from the general population will be recruited. Recruitment will be done in several catchment areas around the research site by collaborating with the local authorities and setting up information sessions to inform potential participants about the study. Potential participants who are interested in initiating hormonal contraception will be invited for a pre-screening visit at the RU Research Clinic.

Upon arriving at the RU Research Clinic, all potential eligible participants will be assigned a participant identification number. The informed consent (IC) process will be done according to the existing GCP-compliant RU IC SOP and will include a group educational session with a video screening, followed by an individual session, consisting of a formal assessment of literacy, a discussion with a nurse counselor and a formal assessment of understanding of the study including the IC procedures.

After written informed consent is obtained by the woman and, in case of women minor of age (<21) and not married by the parent or legal guardian (see section 8.2 for more details), staff will:

- Collect contact information
- Collect menses information.
- Conduct HIV and other STI counseling.
- All consenting, eligible women will be invited for a baseline visit, 4 to 6 weeks after the pre-screening visit. Women who are menstruating at the baseline visit will be rescheduled.

In addition:

- All women included in the clinical trial will be asked at pre-screening whether they agree to possibly participate in a qualitative component of the study i.e. an IDI or a FGD.
- A total of 5 women will be purposively selected initially, and if data saturation is not reached after these 5 interviews, additional women will be selected one by one until data saturation is reached but will not exceed 15 women. Each IDI participant will be asked to provide written informed consent for participation in the IDI. After consent has been given, the participant will be interviewed by a study staff member. The IDIs will help to refine the Interviewer Administered Questionnaires (IAQ) that will be administered to all clinical trial participants at baseline and follow-up visits.

#### 8.1.1.2. Baseline visit (week 0)

First, women will be interviewed face-to-face using an IAQ. The IAQ will include questions about demographic characteristics, sexual behaviour, medical history and reproductive history, current medication, menses information and acceptability of the CVR.

The following procedures will also be carried out:

- A pelvic examination:
  - A total of 3 vaginal swabs will be collected:
    - One cotton swab for Wet Mount [*Trichomonas vaginalis* (TV); *Candida albicans*] and smears for BV diagnosis;
    - Two regular flocked swabs (Copan, Italy) for the characterisation of the vaginal microbiome.
  - A total of 2 cervical swabs will be collected for *Neisseria gonorrhoeae* (NG) and *Chlamydia trachomatis* (CT) testing. One swab will be processed immediately for the rapid detection of CT. The other regular flocked swab will be used for molecular testing of CT/NG.
  - A CVL for the detection of inflammatory processes.
- A physical examination of other body systems will be performed with special attention to the cardiovascular system.
- Collect blood by venepuncture (5 ml) in a serum tube and test for HIV according to the national HIV algorithm, and for syphilis and herpes simplex type 2 (HSV-2).
- A urine sample will be obtained for testing for pregnancy and an aliquot of fixated urine for FISH analysis will be stored at 2-8°C until shipment to ITM.
- All women will be offered risk reduction counselling, including pre- and post-test HIV counselling and condoms free of charge.
- Curable genital infections will be treated at the study site free of charge.
- Any other medical conditions – including newly diagnosed HIV – will be referred to local referral hospitals or clinics.

#### **8.1.2. Enrolment visit (at the start of week 1)**

Women will be invited for the enrolment visit which will take place on the first day of their menstrual cycle. (ie. the first day of menstrual bleeding). A visit window of + 1 day will be allowed when the menstrual cycle starts on a Sunday or bank holiday. The visit can be rescheduled maximum once if the participant is not on her first day of menstrual bleeding (+ 1 day).

All test results from the baseline visit will be reviewed, and eligibility will be confirmed. Eligible women will be randomized either to an intermittent regimen (group A) or an extended (continuous) regimen (group B) of ring use.

There will be no re-screenings.

The following procedures will also be carried out:

- The general physical examination will be performed as at baseline.
- All women will be offered risk reduction counselling and condoms free of charge.
- A urine sample will be obtained for pregnancy testing.
- Study staff will teach women how to use the ring and study participants will be asked to insert the ring while still at the study clinic.

- A questionnaire on acceptability of the ring after the ring has been inserted.
- Participants will receive a diary card and will be explained how to complete a diary card regarding ring use and sexual behaviour as well as how to complete a self-rating adherence scale.
- Provide a follow-up visit date: 3 weeks after the enrolment date.

### 8.1.3. Follow up visits: Visits 2 to Visits 6

The follow up visits are planned to coincide with times of removal and insertion of the ring. Women in group A will visit the clinic at days of removal and insertion. These visits will coincide in group B as the old ring will be replaced by a new one at the same visit.

Participants in group B will be allowed to complete each follow-up visit up to three days prior/after their scheduled visit. The visit window for participants in group A (intermittent use) will depend of the kind of visit. Ring removal visits can be delayed for a maximum of 2 days, ring insertion visits can be performed a maximum of 2 days in advance. Every effort should be made to ensure participants adhere to this visit schedule.

The following procedures are performed at each ring removal visit (both study arms):

- Information on adverse events, social harms and concomitant medication will be collected.
- The pelvic and general physical examinations will be performed as at baseline. A total of 3 vaginal swabs are collected for:
  - One cotton swab for Wet Mount [*Trichomonas vaginalis* (TV); *Candida albicans*] and smears for BV diagnosis;
  - Two regular flocked swabs (Copan, Italy) for the characterisation of the vaginal microbiome.
- At visit 6 for Group A and visit 5 for Group B, after the final ring has been removed and all other vaginal specimens have been collected, a CVL sample will be collected.
- A urine sample is obtained, tested for pregnancy and an aliquot of fixated urine will be stored for FISH analysis.
- A completed diary card will be collected at each visit and a new diary card will be provided. Any problems with ring use will be addressed.
- The removed ring will be processed according to the instructions provided by the ITM and stored for biofilm analysis.
- Risk reduction counselling will be provided as well as condoms (free of charge).
- During the last ring removal visit (V6 for group A and V5 for group B) the following additional procedures will be offered:
  - a Visual Inspection with Acetic acid (VIA) to identify women at risk for cervical cancer;
  - An HIV test according to the national HIV algorithm. A maximum of 5 ml of blood will be collected by venepuncture in a serum tube. Pre- and post-test HIV counselling will be provided.

Additional questionnaires during ring removal visits:

1. The IAQ will be performed at every visit and will assess adherence and acceptability of the ring use but will be more comprehensive at visits 4 and 6 for group A and at visits 3 and 5 for group B. It will also assess factors that might influence the vaginal microbiome and vaginal inflammation.
2. Between weeks 7 and 9, 16-24 women will be enrolled in one of two FGD in each randomization group, for a total of four FGD.

3. At the last ring removal visit, and if funding permits, all study participants will be invited to provide their feedback on experiences with the new contraceptive method, on acceptability and adherence using ACASI.

The following procedures are performed at the ring insertion visits for group A:

- Information on adverse events, social harms and concomitant medication will be collected.
- Risk reduction counselling will be provided as well as condoms (free of charge).

